### Data collection process

| Data type                     | Method of collection                                      |                                                           |
|-------------------------------|-----------------------------------------------------------|-----------------------------------------------------------|
|                               | Gambia                                                    | Vellore                                                   |
| Weight (of the mother)        | Digital Tanita scale                                      | Micro weight electronics. Model: DS415 series             |
| Height (of the mother)        | Leicester height measure, seca 214                        | Stadiometer                                               |
| Blood pressure                | Electronic BP apparatus (Omron Corporation, Tokyo, Japan) | Electronic BP apparatus (Omron Corporation, Tokyo, Japan) |
| Baseline diet consumption     | Dairy consumption questionnaire                           | Dairy consumption questionnaire                           |
| Barriers assessment           | Questionnaire                                             | Questionnaire                                             |
| PA activity monitoring device | Garmin Vivofit 4 fitness band                             | Garmin Vivofit 4 fitness band                             |
| Height (of the baby)          | Infantometer                                              | Infantometer                                              |
| Ultrasound                    | Aloka USI-145                                             | Voluson GE S-8                                            |
| Biochemistry           |                                                           |                                                           |
| Blood glucose                 | Roche Cobas 800 Enzymic (autoanalyser)                    | Roche Cobas 800 Enzymic (autoanalyser)                    |

## 6. PARTICIPANT IDENTIFICATION AND RECRUITMENT

### 6.1. Study Participants

The study will include healthy pregnant women who have at least one “risk-factor” for developing gestational diabetes (see section 6.2 for high-risk definition).

Date and version No: 18th July 2019, Version 4.2

## 6.2. Inclusion Criteria

- Pregnant women, aged  $\geq 18$  years
  - Pregnant women  $\leq 16$  weeks of gestational age
  - In addition to the above, pregnant women should meet at least one of the following criteria for high-risk GDM:
    - Booking BMI  $\geq 25 \text{ kg/m}^2$
    - Age  $\geq 25$  years
    - First-degree relative with diabetes
    - Previous pregnancy with GDM
    - Previous gestation with large baby ( $\geq 3.5 \text{ kg}$ )
    - Previous pregnancy with pre-eclampsia/eclampsia
    - History of PCOD/impaired fasting glucose
  - Not currently on any medications (except iron, calcium or folic acid supplements, thyroxine supplement for hypothyroidism, low dose aspirin for pre-eclampsia)\*
- \*women conceived by ovulation induction using clomiphene citrate or metformin for PCOD will not be excluded from the study.

## 6.3. Exclusion Criteria

The participant may not enter the study if ANY of the following apply:

- GDM diagnosed prior to screening visit based on IADPSG criteria or documented raised HbA1C, i.e., either fasting glucose  $\geq 5.1 \text{ mmol/L}$  or 1h glucose  $\geq 10.0 \text{ mmol/L}$  or 2h glucose  $\geq 8.5 \text{ mmol/L}$ , or a documented HbA1c of  $\geq 6.5\%$  at first booking
- History of pre-gestational diabetes
- Multiple gestation in current pregnancy
- History of severe hyperemesis in the first trimester
- Uncontrolled pre-gestational or gestational hypertension (BP  $> 150/100 \text{ mm Hg}$ ) or on treatment
- History of recurrent (more than two) first trimester spontaneous abortions or stillbirths
- History of significant ante- or post-partum hemorrhage in the previous pregnancy
- Previous child born with congenital anomalies
- Pregnancy following in-vitro fertilization or any assisted reproductive technology and those unwilling to adhere to the study protocol will be excluded from the study
- Previous or current psychiatric illness on medication
- Previous or current neurological condition (e.g. epilepsy) or on medication
- Women meeting absolute contraindications for physical activity during pregnancy as recommended by the ACOG (heart disease, restrictive lung disease, incompetent cervix/cerclage, pregnancies at risk for premature labour, gestational hypertension, severe anaemia)
- Physical disability to PA and/or known lactose intolerance

## 7. STUDY PROCEDURES

The schedule of procedures at each visit is provided below

Date and version No: 18th July 2019, Version 4.2

| Visit                                                 | Study procedures                                                                                                                                                                                                                                                                |
|-------------------------------------------------------|---------------------------------------------------------------------------------------------------------------------------------------------------------------------------------------------------------------------------------------------------------------------------------|
| Screening visit
(≤16 weeks)
(Visit -2) | Height
Weight
Blood pressure (mother)
Antenatal examination (fundal height)
OGTT
Dating Ultrasound scan
Barriers to pregnancy intervention assessment-1                                                                                                       |
| Run-in-phase
(≤17 weeks)
(visit -1)    | Weight
Blood pressure
Antenatal examination (fundal height)
Questionnaire based assessment of background dairy consumption
Diet and PA counselling
Dispensing wearable activity monitors device for assessment of baseline PA for 7-days and compliance testing. |
| Randomization
(≤18 weeks)
(visit 0)    | Weight
Blood pressure
Routine antenatal examination (fundal height)
Randomization                                                                                                                                                                                      |
| Visit 1 (week 18-20)                           | Weight
Blood pressure
Routine antenatal examination (fundal height)
Morphology scan                                                                                                                                                                                    |
| Visit 2 (26-28 weeks)                          | Weight
Blood pressure
Routine antenatal examination (fundal height)
OGTT                                                                                                                                                                                               |
| Visit 3 (32 weeks)
End of Study visit      | Weight
Blood pressure
Routine antenatal examination (fundal height)
Fasting plasma glucose
Ultrasound scan (to monitor foetal growth)
Barriers to pregnancy interventions assessment-2 (for future studies)                                                      |
| Delivery
(post-trial surveillance)         | Weight (mother)
Blood pressure (mother)
Intrapartum outcomes
Neonatal outcomes (Birth length, Birth weight, APGAR score)                                                                                                                                               |
| Telephonic contacts / Home visits              | General well-being
Compliance with interventions (step count from accelerometer, yoghurt pot-count)                                                                                                                                                                          |

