## 5. STUDY DESIGN

**Design:** 2 x 2 factorial design, multi-centric, open labelled, randomized controlled trial

**Total study duration:** 36 months

**Number of scheduled visits:** 5

- (i) **Screening visit (visit -2,  $\leq 16$  weeks GA):** Singleton pregnant women willing to participate in the study will be assessed for eligibility based on inclusion/exclusion criteria and eligible participants will be asked to sign an informed consent if willing to participate. Eligible women will undergo an oral glucose tolerance test (OGTT) to rule out impaired glucose intolerance or diabetes at screening and will also undergo dating ultrasound scan. Routine antenatal examination will be done. Barriers to life-style interventions-1 during pregnancy will be assessed using a questionnaire.
- (ii) **Run-in visit (visit -1,  $\leq 17$  weeks GA):** Baseline assessments of dairy product consumption will be done using standardized questionnaire. Additionally, objective measurements of baseline PA activity over 7 days will be assessed in all study participants (with the result blinded to participants) using a wearable accelerometer device (Garmin Vivofit 4 fitness band).
- (iii) **Randomization ( $\leq 18$  weeks GA):** Women will be randomized to either (i) diet (consumption of 200g of yoghurt per day), (ii) PA (a minimum of 40% increase above the recorded baseline PA) (iii) diet and PA or (iv) standard care. Active intervention will be from randomization to 32 weeks of GA.
- (iv) **Visit 1 (18-20 weeks GA):** maternal weight, blood pressure, routine antenatal examination and foetal morphology scan.
- (v) **Visit 2 (26-28 weeks GA):** maternal weight, blood pressure, routine antenatal examination and OGTT. Primary endpoint (diagnosis of GDM based on IADPSG criteria) will be assessed at this visit. Women with GDM will continue on allocated study intervention until end of study (week 32) in addition to the clinical management provided as per the local obstetric practice.
- (vi) **Visit 3 (32 weeks GA, End of Study visit):** maternal weight, blood pressure, routine antenatal examination, ultrasound foetal scan and fasting blood glucose and barriers to pregnancy intervention-2 assessment. (A repeat ultrasound scan at this stage is based on the evidence that growth restriction although starts in early pregnancy, is more marked between 22-34 weeks and also that foetal measurements do not have

Date and version No: 18th July 2019, Version 4.2

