### Interventions

**Dietary intervention** Each participant in the diet and diet+PA arm will be advised to consume yoghurt 200 g/day once daily prepared locally at the dietary department in CMC, Vellore and from a local production in The Gambia. The yoghurt consumption is independent of the timing of their regular meal time (can be consumed anytime). Record of daily yoghurt and background dairy consumption will be maintained by every participant. The yoghurt will be prepared on a common recipe with the same starter culture at both centres. The yoghurt will be dispensed daily/weekly as feasible by the study centre. Adherence to yoghurt consumption will be monitored on a weekly basis by home visiting field staff. Dietary counselling will be reinforced in all participants and the non-diet arm will not be advised to stop their regular dairy consumption, assuming that any effect on outcome is related to the trial yoghurt consumed.

**Physical activity intervention** Women randomized to the PA and diet+PA arm will be provided PA targets to be followed throughout pregnancy based on their baseline PA assessment which was obtained at run-in-phase. The recommendation will be set based on a minimum of a 40% increase of the baseline step count measured during run-in-phase (refer to section 8.1.2 for details). The daily PA activity will be monitored using an accelerometer device (Garmin Vivofit 4 fitness band) which will provide visual feed back to the participants in the active PA arms in order to motivate participants and help them achieve their daily target step count. All other (yoghurt and standard arm) will also be provided with fitness bands to objectively measure their routine PA behavior throughout the study. However, step counts will be blinded for these participants. Data from these devices will be periodically uploaded using vivohub 2 for compliance monitoring and downloaded to provide visual feedback and counselling to participants.

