#### 7.4. Randomisation

Eligible women will be randomly allocated to one of the following arms (i) Yoghurt (ii) PA (iii) Yoghurt + PA or to the (iv) control group (neither intervention, standard care) following an allocation schedule prestratified for study centre, age and BMI generated by an independent statistician not involved in the study. A variable block randomisation, stratified by centre, and then by age, (<25 and ≥25 years) and BMI (<25 and ≥25 kg/m^2) will be generated, using a password-protected Access database developed by an independent statistician who is not involved with trial participants or data analysis. A unique study ID will be assigned to each participant at screening by the research officer.

In India, the random allocation of each participant to one of the four intervention groups, stratified by age\*BMI will be performed using a computer interface (Access database with forms and data separated into a frontend and password backend, respectively).

In Gambia, due to logistical limitations, separate lists will be generated for each strata combination (age x BMI) and randomisation assigned using opaque, sealed envelopes. As this is an open-labelled study, study participants, and investigators will not be blinded to the treatment arm. Laboratory personnel and the trial statistician will be blinded.

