#### 7.5.2. Baseline assessment at Run-in visit (Visit: -1; week ≤17)

- I. **Weight:** Weight of the mother will be recorded as described in 7.5.1 (II)
- II. **Blood pressure:** Systolic and diastolic BP of the mother will be recorded as described in 7.5.1 (III)
- III. **Antenatal examination (fundal height):** Routine antenatal examination including fundal height will be recorded as described in 7.5.1 (IV)
- IV. **Dairy consumption assessment:** Background dairy product consumption of the study participant will be assessed using standardized questionnaires.
- V. **Safety assessments** to interventions (e.g. adverse events and/or SAE assessment)
- VI. **Concomitant medication** assessment
- VII. **Baseline PA monitoring:** All participants will be advised to wear an accelerometer device to objectively measure baseline PA for next 7 days. The step counts will be blinded (not made visible on the device) in order to avoid influences on routine activity.

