#### 8.1.2.1. Daily walking

"Absolute target" will be calculated as a minimum of a 40% increase from the baseline. This will be calculated as the average of the weekly step count at run-in-phase. Step counts will be monitored using Garmin vivofit 4 band from randomization. Participants will be advised to use the "absolute target" as the minimum reference step count, but try to increase the step count beyond this. Women will be encouraged to perform walking at as speed faster than usual but within the individual's comfort.

Compliance will be calculated based on average step count achieved over a 7-day period including two weekend days. Women achieving at least 80% of the absolute target on a 7-day average will be considered as compliant. Non-compliant participants will be continually motivated and encouraged to achieve their absolute targets either telephonically or by home visits by field workers.

| Baseline
a | 40% increase
b | Minimum
absolute target
(a+b) | 80% of absolute target
(d=a+b) increase
(expected average 1
week step count to be
achieved)
Used to calculate
compliance |
|---------------|-------------------|-------------------------------------|--------------------------------------------------------------------------------------------------------------------------------------------|
| 2500          | 1000              | 3500                                | 3300                                                                                                                                       |
| 3000          | 1200              | 4200                                | 3960                                                                                                                                       |
| 3500          | 1400              | 4900                                | 4620                                                                                                                                       |
| 4000          | 1600              | 5600                                | 5280                                                                                                                                       |
| 4500          | 1800              | 6300                                | 5940                                                                                                                                       |

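### Physical activity counselling for all women at the run-in visit works against the blinded baseline step count that sets each activity target

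*Protocol*

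**What the plan says.** The run-in row of the visit table in Protocol section 7 has two consecutive entries: "Diet and PA counselling" and "Dispensing wearable activity monitors device for assessment of baseline PA for 7-days and compliance testing". Neither is restricted by arm, and none could be, because allocation happens at visit 0.

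Section 7.5.2, on the same visit, says: "All participants will be advised to wear an accelerometer device to objectively measure baseline PA for next 7 days". It then gives the reason for concealing the display: "The step counts will be blinded (not made visible on the device) in order to avoid influences on routine activity". The run-in text in section 5 also has the baseline measured "with the result blinded to participants".

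The baseline then has a working role. In section 8.1.2.1 the activity target "will be calculated as a minimum of a 40% increase from the baseline", and the compliance threshold is derived from that target. Section 5 has the yoghurt and standard-care arms wear the band, display hidden, to "objectively measure their routine PA behavior throughout the study".

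The itemised list in section 7.5.2, the run-in text in section 5 and the schedule in Appendix C show no counselling at visit -1. No section says what the physical activity counselling contains. Dietary counselling is different: the Interventions text in section 5 openly plans it for all participants.

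**The concern.** The plan takes care that the baseline week reflects ordinary behaviour, yet its visit table has staff advise women on activity at the visit that starts that week. Two things are at stake.

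- **The target.** The design intends at least 40% more steps than a woman's usual level. If advice lifts the baseline week, the rule is applied to an already raised figure. The compliance threshold moves with it.
- **The contrast.** For the physical activity main effect, the comparator is the two arms without the activity intervention. If those women have also been counselled, the comparison becomes targets and feedback on top of advice versus advice alone. That may be a smaller difference than activity versus no activity advice.

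**Working it through.** **1. Timing.** Randomisation is at visit 0, so an item at visit -1 reaches women who later enter all four arms. The recording covers the seven days after visit -1. Counselling therefore falls before the recorded days whatever the order of items within the visit.

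**2. The plan's own figures.** Section 8.1.2.1 gives target = 1.4 × baseline. Its worked example is 1.4 × 6,000 = 8,400, which agrees. For a baseline of 5,000, 1.4 × 5,000 = 7,000, as tabulated. The compliance column for 5,000 shows 6,600, which is 5,000 + 0.8 × 2,000, or 1.32 × baseline. The sentence above the table, 80% of the absolute target, would give 0.8 × 7,000 = 5,600, or 1.12 × baseline. That difference is a separate matter. Under either reading the threshold is a fixed multiple of baseline.

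**3. Effect of a raised baseline.** Let r be the proportional rise in steps in the baseline week caused by counselling. The Protocol gives no value, so 0%, 5%, 10% and 20% are assumed. Then

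target / routine = 1.4 × (1 + r)

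and the tabulated compliance threshold / routine = 1.32 × (1 + r).

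For a woman whose routine is 5,000 steps:

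| r (assumed) | Recorded baseline | Target | Target above routine | Tabulated compliance threshold |
|---|---|---|---|---|
| 0% | 5,000 | 7,000 | 40% | 6,600 |
| 5% | 5,250 | 7,350 | 47% | 6,930 |
| 10% | 5,500 | 7,700 | 54% | 7,260 |
| 20% | 6,000 | 8,400 | 68% | 7,920 |

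**4. The contrast.** No arithmetic is possible. The Protocol gives neither the content of the counselling nor its effect on steps or on gestational diabetes. Any effect on the contrast need not run one way: a higher target, if met, widens the step difference between arms, while advice to the comparator arms narrows it.

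**The case against.** Several points on the other side are sound.

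- **The content is undefined.** The entry might mean general antenatal advice or instructions on wearing the band. The values of r above are therefore illustrations. Still, the table lists counselling separately from dispensing the device, and an undefined activity talk at this visit is what the concealed display cannot guard against.
- **40% is a minimum.** Women are told to try to exceed it, so a target above 40% over routine does not breach the rule. It does mean that the minimum asked of each woman, and the threshold for calling her compliant, rest on a distorted reference.
- **Omission elsewhere is weak evidence.** Appendix C is not exhaustive: it also leaves out the safety and concomitant-medication checks. Section 7.5.2 lists baseline assessments, and counselling is not one. A reader might infer that the sections contradict each other on whether counselling happens. The text shows only that they are not aligned.
- **The control definition is not strictly contradicted.** A reader might infer that counselling breaches "control group (neither intervention, standard care". Section 8 defines the interventions as daily trial yoghurt and as target-based walking with group sessions. One talk before allocation is neither.
- **Diet counselling is shared by design.** Section 5 plans it for everyone, so that half of the entry is no defect.

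The conflict between activity advice and a baseline blinded to protect routine activity survives all of these.

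**Conclusion.** Followed as written, the visit table undercuts the Protocol's own safeguard for the baseline week. That conclusion rests on the text alone. Its size is not known: the targets of 47%, 54% and 68% above routine hold only under assumed rises of 5%, 10% and 20%, and if counselling does not change steps the target is unaffected.

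The effect on the contrast is a possibility, not a demonstrated loss. A reader might infer that randomisation is compromised. It is not, because advice given before allocation is balanced across arms; what may change is the comparison being made. A reader might also infer a fall in power. The documents support no such figure, since it would need an assumed share of the activity benefit to come from counselling alone. If the planned 33% reduction is over and above such advice, there is no loss at all.

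This is an inexpensive correction worth making, not a flaw that threatens the trial's validity.

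**What to change.** 1. In the section 7 visit table, remove the physical activity part of the counselling entry at visit -1. Leave only instructions on wearing the band, alongside the planned dietary counselling.
2. Start physical activity counselling at visit 0, after allocation, in the PA and Yoghurt + PA arms only.
3. Make section 7, section 7.5.2 and Appendix C agree on what is done at visits -1 and 0.
4. If general antenatal activity advice is part of standard care, give it to all women after the baseline week and describe it as standard care. This protects the baseline but not the contrast, because the comparator arms still receive activity advice.

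The cost is moving one schedule item by about a week and aligning three places in the Protocol. No extra visits, data or staff are needed.
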